### Planned Data Analysis

This clinical study focuses on the characterization and initial validation of an experimental medical diagnostic test under development. To avoid bias, the physicians involved in diagnosing and selecting the study groups will not participate in the analysis. Furthermore, missing data will not be imputed. In addition, indeterminate index test or reference standard results will not be allowed, as a positive or negative diagnosis will be required according to the previously defined cutoffs. Analyses will be performed on complete cases within each analysis set. The planned sample size (Multimedia Appendix 1) includes a margin for nonevaluable data (10% added for nonassessable data-complete-case analysis). No interim analyses or stopping rules are planned.

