#### Hypotheses

The primary hypothesis, though involving 3 participant groups, focuses on demonstrating a minimum diagnostic performance to distinguish between the ADHD group as a whole and the pediatric control group. Regarding the true positive fraction (true positive fraction [TPF] or sensitivity), due to its high acceptability threshold (TPF_0_=0.90), a noninferiority test will be used for this dimension, with a noninferiority margin of δT_0_=−0.10. Since the primary objective is to determine whether the index test yields classification probabilities—TPF and false positive fraction (false positive fraction [FPF] or 1-specificity)—that are minimally acceptable (TPF_0_ and FPF_0_), the corresponding hypothesis, considering the noninferiority assumption for sensitivity, can be formally stated as:

(1)$$H_{0}:\left\{TPF-TPF_{0}\leq \delta \;\overset{T}{\underset{0}{\cup }}FPF\geq FPF_{0}\right\}$$

If H_0_ can be rejected, TPF−TPF_0_ > δ$\begin{array}{c} T\\ 0 \end{array}$ and FPF<FPF_0_; therefore, the index test would be noninferior to a hypothetical test with 90% sensitivity and superior to a hypothetical test with a specificity of 1−FPF_0_.

Two additional pairwise comparisons will be conducted: one between each ADHD group and pediatric controls, and another between the ADHD groups themselves, with hypotheses formulated as previously described. The Hochberg procedure will be used to control Type I error [70].

Biomarker identification will use dimensionality reduction methods, which are descriptive and do not require hypothesis testing or multiplicity adjustments.

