#### Analysis of Primary Parameters

The analysis of diagnostic accuracy requires preliminary analyses to identify biomarkers that optimize the diagnostic performance and to develop a classification algorithm based on biomarker values across the three study groups defined by the clinical team, serving as the reference test. The first secondary parameter, essential for evaluating the primary parameter, will also be analyzed in a confirmatory fashion without explicit hypothesis testing.

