#### Diagnostic Performance of the Index Test

The primary parameters are the classification probabilities of the index test relative to the reference test. In addition to these classification probabilities, positive and negative predictive values (PPV and NPV, respectively) and diagnostic likelihood ratios will be calculated. Inferences will be made by calculating 95% asymmetric rectangular confidence regions for each pair of interest values (TPF and FPF), (PPV and NPV), and (DLR^+^ and DLR^−^). Confidence regions will be calculated from the cross-product of the 97.5% confidence intervals of each component in each pair. Sensitivity values will be assessed for noninferiority (and potentially superiority), while specificity will be evaluated for strict superiority. In addition to naive predictive value estimates, which will be biased by design, other estimates will be adjusted using external prevalence data and diagnostic likelihood ratios or Bayesian multiplication factors to mediate prior and posterior probabilities:

, (2)$$logit\;PPV=logit\;\rho +\log{DLR}^{+}$$

, (3)$$logit\;NPV=-logit\;\rho \;+\;-\log{DLR}^{-}$$

where ρ is the prevalence in the target population (7.0% [71]). Clinical information and reference standard results will not be available to the performers of the index test. Furthermore, the reference standard will be performed after the index test. Moreover, performers of the index test will neither be involved in the technological processing nor the statistical analyses of either the index or the reference standard tests. Finally, cross-tabulation of the index test results (or their distribution) by the results of the reference standard will be considered.

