### Strengths and Limitations

The study included primarily right-handed children (10% left-handed) aged 7‐12 years who could suspend medication and tolerate EEG recording sessions. The inclusion of left-handed children, up to 10% of eligible participants (Table 1), partly addressed this limitation within the study. Despite excluding children with ASD or other comorbidities, the sample of this study is fairly representative of most ADHD populations. However, the team is planning future studies to examine biomarker performance in more heterogeneous, clinically representative ADHD populations, including children with common comorbidities, such as ASD.

Another limitation was that the final clinical diagnosis made by the PI was used as the reference test, as well as to define the participant grouping for algorithm training, thus introducing some circularity that could inflate diagnostic accuracy. However, several measures were introduced in order to mitigate this issue: first, the PI established the diagnosis independently, following established clinical criteria and without knowledge of any algorithmic or EEG outputs, thereby reducing the risk of circularity; second, several patients were previously diagnosed by other professionals, and the PI only confirmed the ADHD diagnosis; and third, a contract research organization was hired and an external neuropsychologist independently evaluated all patients.

Despite the aforementioned limitations, the study also presents notable strengths. First, it benefits from a large sample size, which enhances the reliability of the findings and supports the generalization of the results and allows for comparisons between ADHD subtype groups. Additionally, it incorporates a comprehensive neuropsychological assessment that enables a detailed examination of participants’ cognitive profiles. This approach allows for a more accurate identification of the specific neurocognitive processes affected in children with ADHD, providing a robust dataset that can inform future research and support the exploration of other clinical and neurodevelopmental aspects of the disorder across different ages.

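### Biomarkers and classifier are developed on the same study groups that supply the confirmatory sensitivity and specificity test, and the article's reason for keeping selection out of the inference is faulty

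*Protocol article*

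**What the plan says.** In the Protocol article, Analysis of Primary Parameters states the order of work: "The analysis of diagnostic accuracy requires preliminary analyses to identify biomarkers that optimize the diagnostic performance and to develop a classification algorithm", using biomarker values across the three study groups. Statistical Analysis calls biomarker identification and the accuracy objective interdependent.

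Hypotheses sets a formal test on those groups. For sensitivity, "due to its high acceptability threshold (TPF_0_=0.90), a noninferiority test will be used for this dimension", "with a noninferiority margin of δT_0_=−0.10". For specificity, the index test must be "superior to a hypothetical test with a specificity of 1−FPF_0"; the article gives no number for FPF0. Diagnostic Performance of the Index Test describes the inference: "Confidence regions will be calculated from the cross-product of the 97.5% confidence intervals of each component in each pair".

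On selection, Hypotheses says: "Biomarker identification will use dimensionality reduction methods, which are descriptive and do not require hypothesis testing or multiplicity adjustments". Statistical Analysis repeats that multiplicity adjustment is unnecessary because this aim involves no hypothesis test.

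Two further places matter. Planned Data Analysis rules out indeterminate results, "as a positive or negative diagnosis will be required according to the previously defined cutoffs". Strengths and Limitations says that the principal investigator's diagnosis was "used as the reference test, as well as to define the participant grouping for algorithm training, thus introducing some circularity" that could inflate accuracy. It lists three mitigations: a diagnosis made without sight of EEG output, earlier diagnoses by other professionals, and an independent external neuropsychologist.

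**The concern.** Choosing features because they optimise sensitivity and specificity, and then testing sensitivity and specificity in the same children, is not a neutral descriptive step. It changes the null distribution of the test. The article accepts that the two aims depend on each other, yet treats selection as having no bearing on the inference because it is not itself a hypothesis test. The second statement does not follow from the first.

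The stated safeguards do not fill the gap. All three mitigations protect the independence of the label; none keeps the children used for training apart from those used for testing. Cut-offs described as already defined are hard to reconcile with an algorithm still to be developed.

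At stake is the primary claim. Without separation, an algorithm with little or no diagnostic value could meet both criteria. The expected advantage over the CPT-3 would also be flattered, since the CPT-3 cut-off is generated by its own program and not tuned here.

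**Working it through.** **1. Does the sample size set children aside for training?** Inputs are from Third Visit: 40 per group from the calculation, 10 more per group to explore factors influencing performance and SCT validity, and 10% for nonassessable data.

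- 3 × 40 = 120; 120 × 1.10 + 3 × 10 = 162. This reproduces the stated total, with the 10% applied to the 120 only.
- Every child is accounted for, and none is allotted to training. The 120 itself cannot be rebuilt, because FPF0, the assumed true values and the power are not in the article.

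**2. The sensitivity rule.** The null sensitivity is 0.90 − 0.10 = 0.80. Reading each 97.5% interval as two-sided with equal tails gives one-sided 0.0125 per component. The critical count r is the smallest with P(X ≥ r | n, 0.80) ≤ 0.0125. Case numbers are 2 × 40 = 80, 2 × 50 = 100 and 2 × 54 = 108. The last two columns take true sensitivity as 0.80 and treat the apparent count as binomial at 0.85 or 0.90.

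| Cases | r | Exact type I error | Pass probability, optimism 0.05 | Pass probability, optimism 0.10 |
|---|---|---|---|---|
| 80 | 73 | 0.005 | 0.07 | 0.45 |
| 100 | 90 | 0.006 | 0.10 | 0.58 |
| 108 | 96 | 0.011 | 0.16 | 0.72 |

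If the intervals were one-sided (0.025), 108 cases would need 95 positives and the last three entries would be 0.021, 0.24 and 0.81. A small optimism is enough to undo the error control on this component.

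**3. How large could the optimism be?** Simulation with 80 cases, 40 controls and independent features carrying no signal. Features were selected by univariate group difference, followed by a linear discriminant and a Youden cut-off, with 150 repeats per setting. Feature counts are assumptions; 2016 is 64 × 63 / 2, the number of electrode pairs. Entries are sensitivity/specificity.

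| Candidates, kept | Same children | Nested 5-fold | New subjects |
|---|---|---|---|
| 100, 10 | 0.77/0.77 | 0.59/0.39 | 0.59/0.41 |
| 500, 20 | 0.90/0.90 | 0.64/0.37 | 0.62/0.38 |
| 2016, 20 | 0.94/0.93 | 0.66/0.34 | 0.65/0.35 |

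A useless test has sensitivity + specificity = 1, and the nested estimates recover that closely. A pass needs 73 of 80 cases positive and, of 40 controls, 32, 35 or 38 negative for assumed specificity thresholds of 0.60, 0.70 or 0.80. With 2016 candidates and 20 kept, the false-pass rate under reuse was 81%, 74% and 31%. Over nine settings (100, 500 or 2016 candidates; 5, 10 or 20 kept) it ran from 0% to 81%. With nested cross-validation it was 0% in all of them.

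**4. Sensitivity to the selection method.** With 110 cases, 55 controls, 2016 noise features and the cut-off set at 90% sensitivity on the same data, keeping the top 20 features by group difference gave an apparent FPF of 0.15. A useless test would give 0.90. Replacing that selection with unsupervised principal components gave 0.82, 0.76, 0.68 and 0.54 for 5, 10, 20 and 40 components. Optimism remains but is far smaller.

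**5. Would a simple split rescue the design?** Holding out one third of 108 cases leaves 36. The rule then needs 35 of 36, and power at true sensitivity 0.90 is 36 × 0.9^35 × 0.1 + 0.9^36 = 0.11. This sample size does not support a plain hold-out.

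**The case against.** The strongest reply is that the article never says accuracy will be computed on the training data. Cross-validation and tuning are details that a condensed article commonly leaves to the full protocol, the sample-size appendix or the analysis plan, none of which is shown. That stands: the bias is conditional, and silence does not prove absence. What remains is a stated rationale that is wrong whatever those documents contain.

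A reader might infer four stronger things that the text does not support.

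- That the plan declares no correction for overfitting to be needed. It waives multiplicity adjustment only.
- That the cut-off is tuned on these children. The article says it is previously defined, in a sentence covering both index test and reference standard. That is unclear, but it is not evidence of tuning.
- That the intervals are ordinary binomial ones. No interval method is named.
- That the authors admit to testing on the training children. The circularity they admit is one diagnosis serving as both training label and reference test.

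The simulated sizes are also open to challenge. The article speaks of dimensionality reduction, and with unsupervised components the optimism is much smaller. On the other hand, selecting biomarkers to optimise performance suggests that outcome information is used. Finally, the article calls the work an initial validation of a test under development, and keeps the EEG-processing team from diagnoses during data collection. Neither separates training from testing.

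**Conclusion.** The point holds in conditional form. The article ties the confirmatory test to biomarkers and a classifier developed on the same three groups, sets no children aside for training, and gives an unsound reason for treating selection as irrelevant to the inference. Unless selection and training are separated from testing, primary TPF and FPF will be optimistically biased and the confidence region will fall short of its nominal coverage.

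The direction does not depend on the simulation settings. The magnitude does: it rests on assumed feature counts, independent features, a simple classifier and, for the false-pass rates of 0% to 81%, supervised selection and assumed specificity thresholds. These figures illustrate what could happen; they do not estimate the bias in this study. Because the primary claim depends on the answer, it should be settled before the analysis.

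**What to change.** - Define primary TPF and FPF as out-of-sample quantities. Refit feature selection, any outcome-informed dimension reduction, tuning and the cut-off inside each training fold of a nested cross-validation, and compute TPF and FPF from outer-fold predictions only. Alternatively, lock the algorithm and test it on independent children.
- Use intervals that reflect refitting of the whole pipeline; ordinary binomial intervals are only approximate for cross-validated estimates.
- Replace the rationale in Hypotheses and Statistical Analysis with a statement that biomarker selection affects the confirmatory test.
- State when, and on what data, the index-test cut-off is fixed.
- Call a nested result internally validated only. If training and testing are not separated, label the primary result exploratory.
- If the full protocol or analysis plan already specifies this, say so in the article and align the wording.

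The nested option costs computing time and text changes, with no new participants. Reported accuracy will probably be lower and its intervals wider. Testing on independent children would need further recruitment.

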#### Statistical Analysis

The primary objective will be to assess the diagnostic accuracy of the index test in terms of classification probabilities, specifically sensitivity and specificity. Sample size calculation ensures a minimum performance threshold within the target population.

This objective is interdependent with another primary aim, identifying the minimal set of biomarkers that optimize the diagnostic performance of the index test. As this objective does not involve hypothesis testing, adjustments for multiplicity are unnecessary.

The analyses of the secondary objectives will be exploratory, except for the first, which shares the hypothesis-free nature of biomarker identification. Tertiary objectives will also be exploratory, focusing on the validity of the SCT construct and EEG signal preprocessing systems. These analyses may be expanded in future studies to identify EEG-based clusters associated with ADHD symptomatology.

#### Analysis of Primary Parameters

The analysis of diagnostic accuracy requires preliminary analyses to identify biomarkers that optimize the diagnostic performance and to develop a classification algorithm based on biomarker values across the three study groups defined by the clinical team, serving as the reference test. The first secondary parameter, essential for evaluating the primary parameter, will also be analyzed in a confirmatory fashion without explicit hypothesis testing.

#### Diagnostic Performance of the Index Test

The primary parameters are the classification probabilities of the index test relative to the reference test. In addition to these classification probabilities, positive and negative predictive values (PPV and NPV, respectively) and diagnostic likelihood ratios will be calculated. Inferences will be made by calculating 95% asymmetric rectangular confidence regions for each pair of interest values (TPF and FPF), (PPV and NPV), and (DLR^+^ and DLR^−^). Confidence regions will be calculated from the cross-product of the 97.5% confidence intervals of each component in each pair. Sensitivity values will be assessed for noninferiority (and potentially superiority), while specificity will be evaluated for strict superiority. In addition to naive predictive value estimates, which will be biased by design, other estimates will be adjusted using external prevalence data and diagnostic likelihood ratios or Bayesian multiplication factors to mediate prior and posterior probabilities:

, (2)$$logit\;PPV=logit\;\rho +\log{DLR}^{+}$$

, (3)$$logit\;NPV=-logit\;\rho \;+\;-\log{DLR}^{-}$$

where ρ is the prevalence in the target population (7.0% [71]). Clinical information and reference standard results will not be available to the performers of the index test. Furthermore, the reference standard will be performed after the index test. Moreover, performers of the index test will neither be involved in the technological processing nor the statistical analyses of either the index or the reference standard tests. Finally, cross-tabulation of the index test results (or their distribution) by the results of the reference standard will be considered.

### Ethical Considerations

This study was approved by the Research Ethics Committee of the HUPHM on February 13, 2023 (PI 207/22). Informed consent was obtained from legal guardians and assent from minors, in accordance with the provisions of Organic Law 3/2018 of December 5 [72], on the Protection of Personal Data and Guarantee of Digital Rights. All procedures involving human participants were conducted in accordance with the ethical standards of the responsible institutional and national research committee and with the 1964 Declaration of Helsinki and its subsequent amendments. Monitoring of the clinical trial was carried out as required by applicable clinical research regulations. Privacy was always guaranteed. All participants had a secret code which was dissociated and saved separately from personal identification data. All participants entered into the study without compensation. All data generated or analyzed will be fully anonymized to ensure participant confidentiality (ISRCTN Registry ISRCTN12110752).

### Risks and Adverse Events

Any adverse events from the EEG recordings, index task, and neuropsychological tests will be recorded according to the clinical guidelines established in the legal framework. Adverse events will be recorded from the first visit to the last. The researcher ([name]) will assess the association between the events and the assessment and report this to the research ethics committee.

### Data Management

Data will be collected using a pre-established standardized variable form and entered in a password-protected electronic database with role-based access control. Data quality will be ensured through predefined regular monitoring and periodic audits to identify missing or inconsistent entries. Access to the final dataset will be restricted to authorized members of the research team.

## Results

The SINCRONIA study began screening and recruitment in March 2023. Recruitment ended on December 11, 2024. A total of 165 eligible participants were enrolled. This research was funded by the sponsor, Bitsphi Diagnosis. The SINCRONIA study was registered in the ISRCTN Registry, a primary clinical study registry recognized by the World Health Organization (Trial registration: ISRCTN12110752; February 20, 2025).

## Discussion

### Comparison With Prior Work

EEG has been extensively employed to explore various neurophysiological metrics in ADHD, such as power spectral densities and event-related potentials. For instance, Clarke et al [73] demonstrated that children with ADHD exhibit increased theta band activity, decreased alpha band activity, and an elevated theta/beta ratio (TBR) compared to controls. Furthermore, these differences persisted into adulthood, with individuals showing lower beta levels in specific regions and a reduction in the ratio in ADHD compared to controls in recordings with eyes closed [74]. Similarly, Jarret et al [75] found increased relative theta power in the T5 and F7 regions in individuals with ADHD, aligning with findings from Chutko et al [76], who observed elevated TBR in children with both ADHD and SCT. Despite these promising findings, the utility of metrics like TBR as a robust diagnostic tool has been questioned due to inconsistent results [77,78], although in recent years researchers have increasingly favored the use of TBR in combination with Bayesian Gaussian models [79].

Although EEG power metrics offer valuable insights, recent studies have shifted focus toward functional connectivity analyses, which may serve as more stable and reliable biomarkers for ADHD. McNorgan et al [80] identified impairments in functional connectivity within the default mode network, reinforcing the hypothesis that ADHD involves disrupted brain networks underlying attention and executive control. Michelini et al [81] further highlighted abnormalities in the corpus callosum and connectivity between the default mode network and frontoparietal/salience networks, suggesting that ADHD is fundamentally a disorder of brain connectivity and providing critical insights by examining brain connectivity across controls, individuals with persistent ADHD, and those in remission. Their findings revealed that individuals with ADHD exhibited less pronounced increases in theta band connectivity following cognitive control tasks, indicating deficits in modulating connectivity during transitions from rest to task-oriented states. Additionally, during the Flanker task, those with ADHD demonstrated global hyperconnectivity in theta, alpha, and beta bands when the task’s prestimulus cues were incongruent and only showed hyperconnectivity in the beta band during the processing of target stimuli when the stimuli were congruent, which correlated with poorer cognitive control and dysfunctional behavior [81]. These findings are consistent with previous research showing enhanced connectivity in the alpha and beta bands during attention tasks [36,82].

Despite recent advancements, significant limitations persist in the literature. Many studies rely on small sample sizes and predominantly male samples or fail to report sex distribution, limiting the generalizability of their findings [81,83,84]. Furthermore, individual biomarkers often explain only a small fraction of the variance in treatment responses, highlighting the need for multifactorial and integrative approaches.

In addition, several methodological issues remain unaddressed in previous studies. Most existing tasks used for biomarker discovery are not grounded in theoretical models of attentional functioning and do not incorporate inhibition as a core element of the pathology, despite its central role in ADHD-related executive dysfunction [7]. These studies also tend to overlook functional connectivity at the source level and instead rely on scalp-level analyses, which limits the spatial precision and neural interpretability of their findings [45]. Moreover, EEG-based investigations are rarely validated against higher spatial resolution techniques such as magnetoencephalography, which could serve as a useful benchmark for signal source validation [47]. Finally, many studies use binary group comparisons (ADHD vs controls), neglecting the added value of including subtypes or differential diagnoses such as SCT and dyslexia in a 3-group design, which would allow for more clinically informative models [44,85].

Our study targets to address these gaps by using functional connectivity patterns, derived from EEG signals in the frequency domain, as biomarkers for ADHD. In this study, which will include at least 165 participants, we seek to improve the diagnostic accuracy achieved in the clinic at the time of this writing and to differentiate ADHD subtypes or other comorbid conditions that might be potentially confused with ADHD, using EEG-based ML algorithms applied to a go/no-go task. This study’s strength lies in its comprehensive design and robust sample size, enabling the identification of ADHD with high accuracy.

By integrating EEG connectivity metrics with ML algorithms, we aim to uncover reliable biomarkers for ADHD, advancing the field and contributing to a deeper understanding of this neurodevelopmental disorder.

